## 6 STUDY DESIGN

### 6.1 Overall Study Design and Plan

#### 6.1.1 Study design

This is a phase 4 multicentre, open-label study of amyloid PET imaging of participants who have one of the following syndromic diagnoses: SCD-plus, MCI, or dementia where AD is in the differential diagnosis. Participants will be randomised to 3 arms. Arms 1 and 2 allow testing the impact of amyloid PET on diagnostic confidence, patient management, and ultimately decision making and the cost-effectiveness of dementia care. Arm 3 allows to investigate the optimal timing of amyloid PET imaging in the diagnostic workup.

The baseline visit must take place within 14 days after the screening visit and can be combined with the screening visit. At baseline, the investigator will record the syndromic diagnosis made by the managing physician, the managing physician's confidence in that diagnosis, and the managing physician's estimate of the likelihood that the patient's symptoms are due to AD. (According to [\[Johnson et al, 2013\]](#), the managing physician is a dementia expert trained and board-certified in neurology, psychiatry, or geriatric medicine who devotes a substantial proportion [at least 25%] of patient contact time to the evaluation and care of adult acquired cognitive impairment or dementia.). The investigator and the managing physician may be but do not have to be the same person. Participants will be stratified by syndromic diagnosis (SCD-plus, MCI, or dementia) and then randomly assigned (1:1:1) to 1 of 3 arms:

- **Early Amyloid PET Arm:** Participants will undergo amyloid PET imaging within 4 weeks after the baseline visit. Amyloid PET will be carried out with high priority over other diagnostic exams except MRI in the early amyloid PET arm. The results of the scan must be communicated to the managing physician as soon as available. Early Amyloid PET arm participants will undergo an optional second amyloid PET scan within at 12 to 18 months window after the initial scan.
- **Late Amyloid PET Arm:** Participants will undergo amyloid PET imaging at 8 months ( $\pm 8$  weeks) after baseline.
- **Free Choice Arm:** The managing physician will decide whether the participant undergoes amyloid PET imaging. The imaging can be done at any time within 12 months after baseline. The reason for the choice will be collected.

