## **9.6 Amyloid PET for Late Amyloid PET Arm, 8 Months ( $\pm$ 8 Weeks After Baseline)**

All female participants of childbearing potential must have a negative pregnancy test before the imaging study is done. The participants in the Late Amyloid PET arm of the study will undergo amyloid PET imaging at 8 months ( $\pm$ 8 weeks) after baseline. Amyloid PET scan must take place after the T2 visit at 6 months  $\pm$  14 days.

If the managing physician chooses to order amyloid PET imaging for the participants in the Free Choice arm, those participants may undergo the imaging at any time from baseline to 12 months after baseline.

The following will be recorded for all participants who have undergone amyloid PET imaging:

- Review of current medications
- Amyloid PET scan results
- All AEs that occurred within 48 hours of study drug administration
- All SAEs occurring within 30 days of study drug administration

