#### 10.1.2 Secondary endpoints

The timepoints are defined as follows:

- T0 = baseline,
- T1 = 12 weeks after T0,
- T2 = 6 months ( $\pm 14$  days) after T0,
- T3 = 13 months ( $\pm 4$  weeks) after T0;
- T4 =  $\leq 28$  days after the optional second scan, which will be 12 to 18 months after T0.

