##### 10.1.2.1 Diagnosis and confidence

- The difference between the Early Amyloid PET arm and Late Amyloid PET arm in the time to communicate to the patient an etiologic diagnosis with very high confidence ( $\geq 90\%$ ).
- The changes in the managing physician's etiologic diagnosis at T3 vs T2 vs T1 in each arm.
- The changes in the managing physician's diagnostic confidence at T3 vs T2 vs T1 vs T0 in the Early Amyloid PET vs Late Amyloid PET arms.
- The managing physician's estimate of the likelihood that the patient's symptoms are due to AD at T3 vs T2 vs T1 vs T0 in the Early Amyloid PET arm vs the Late Amyloid PET arm.
- Changes over calendar time in the placement of amyloid PET imaging in the patient workup for participants in the Free Choice arm.

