### **10.3.17 Management plan**

The management plan (pharmacologic and nonpharmacologic) made by the managing physician at T1, T2, and T3 will be recorded in the eCRF. Pharmacologic management may include cognitive enhancers (acetylcholinesterase inhibitors, memantine, ginkgo biloba, and others [including nutraceuticals]), selective serotonin reuptake inhibitors, benzodiazepines, hypnotics, and neuroleptics (typical and/or atypical). Nonpharmacologic management may include cognitive rehabilitation, validation therapy, psychoeducation of family members, nutritional intervention, physical activity programmes, occupational therapy, and others.

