### **12.5.3 Handling of missing values/censoring/discontinuations**

The reasons for incomplete data are many and include major protocol deviations, dropout because of study withdrawal or death, non-attendance at clinical visits, missing questionnaire items, uninterpretable images, etc.

The primary efficacy analysis will be conducted on the PPS population, which is based on complete cases.

Secondary efficacy analyses will be conducted on the FAS population. In time-to-event analyses, dropout and major protocol deviations are accounted for by censoring at the time of dropout or protocol deviation. In cross-sectional analyses and analyses of change between 2 timepoints, only complete cases will be included. Cases with a major protocol deviation before the first timepoint in the cross-sectional or change analysis will be excluded. The longitudinal mixed-effect analyses will be based on the observed cases. Data will be censored after a major protocol deviation. The underlying assumption in all analyses is that missing data are missing at random and not related to the primary outcome.

The proportion of missing data at each time point will be computed for the Early Amyloid PET, Late Amyloid PET, and Free Choice arms separately, and stratified for SCD Plus, MCI, and dementia.

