## **12.6 Secondary Analyses**

### **12.6.1 Secondary efficacy variables**

In the analyses of the secondary efficacy variables, a cross-sectional difference between arms in a secondary endpoint at T1, T2, T3, or T4 (see Table 1) will be carried out by a chi-squared test if the endpoint is dichotomous, a 2-sided *t*-test if the endpoint is normal, and Mann-Whitney test if the endpoint is categorical or continuous and non-normal. The effect of baseline characteristics such as age, gender, MMSE, etc will be studied by a linear or logistic regression model.

A difference between study arms in the longitudinal change of a secondary endpoint will be tested by means of logistic or linear regression where the first measurement is a covariate (ANCOVA analysis) and the second measurement is the outcome. Differences in longitudinal

trends between arms will also be examined by means of the mixed-effects regression model. The effects of baseline characteristics such as age, gender, MMSE, etc. will be studied by including them in the regression models.

All tests will be 2-sided and the significance level will be set at 5%. Bonferroni corrections for multiple testing will be applied when appropriate. Point estimates will be presented together with 95% Wald confidence intervals. A 95% non-parametric confidence interval will be constructed if the estimate is non-normal.

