#### **12.6.1.1 Diagnosis and Confidence**

- A difference between the Early Amyloid PET arm and the Late Amyloid PET arm in the time to communicate an etiologic diagnosis with a confidence  $\geq 90\%$  will be tested by the log-rank test. The cumulative incidence of diagnoses will be estimated with the Kaplan-Meier method.
- Changes in the managing physician's etiologic diagnosis at T3 vs T2 vs T1 in each arm
- The changes in the managing physician's diagnostic confidence at T3 vs T2 vs T1 vs T0, for participants in the Early Amyloid PET arm vs participants in the Late Amyloid PET arm
- The managing physician's estimate of the likelihood that the patient's symptoms are due to AD at T3 vs T2 vs T1 vs T0 in the Early Amyloid PET arm vs the Late Amyloid PET arm.
- Changes over calendar time in the placement of amyloid PET imaging in the patient workup for participants in the Free Choice arm. The Free Choice arm will be divided into 3 equal-sized groups, according to the date of randomisation. For the Free Choice arm, a change in the placement of amyloid PET imaging over time in the diagnostic workup will be tested by a log-rank test.

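### For change between visits starting at T1 or T2, the planned ANCOVA adjusts for a value taken after randomisation and the Early scan, so its arm coefficient is not the arm difference in change

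*Protocol*

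**What the plan says.** Section 12.6.1, repeated in the synopsis under Secondary Efficacy Analyses, tests a between-arm difference in the longitudinal change of a secondary endpoint by linear or logistic regression "where the first measurement is a covariate (ANCOVA analysis) and the second measurement is the outcome". The covariate is not defined as baseline or T0. Section 12.5.3 treats the method as general: "In cross-sectional analyses and analyses of change between 2 timepoints, only complete cases will be included".

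The endpoints span several visits. Section 10.1.2.1 lists "The changes in the managing physician's diagnostic confidence at T3 vs T2 vs T1 vs T0 in the Early Amyloid PET vs Late Amyloid PET", and section 12.6.1.1 repeats it as "diagnostic confidence at T3 vs T2 vs T1 vs T0, for participants in the Early Amyloid PET arm" against the Late arm. The likelihood that symptoms are due to AD is compared over the same four timepoints. The management plan has no baseline value: under section 10.3.17 it is the plan "made by the managing physician at T1, T2, and T3 will be recorded in the eCRF", and Table 1 has no T0 entry for it.

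The scan timing fixes which measurements precede the intervention. In the Early arm, "Participants will undergo amyloid PET imaging within 4 weeks after the baseline visit" (section 6.1.1), and "T1 = 12 weeks after T0" (section 10.1.2). In the Late arm, "Amyloid PET scan must take place after the T2 visit at 6 months" (section 9.6).

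Section 12.6.1 also plans cross-sectional arm comparisons at each timepoint and a mixed-effects regression for longitudinal trends.

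**The concern.** Adjusting for a first measurement is sound when it was taken before randomisation, because the arms then differ on it only by chance. T1 and T2 are different. They follow randomisation and the Early scan but precede the Late scan. If PET raises diagnostic confidence, which is the trial's hypothesis, the arms differ systematically on T1 and T2.

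A regression of the T2 value on arm and the T1 value compares Early and Late patients who have the same post-scan T1 value. Its arm coefficient is neither the difference in change from T1 to T2 nor the difference at T2. A one-off gain by T1 that is simply held could be reported as a continuing gain, and a Late arm that catches up after its own scan could be shown as catching up by less than it did. For a trial comparing early with late imaging, when the effect arises and whether it is later matched are central to interpretation.

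**Working it through.** **Inputs from the protocol.** Early scan within 4 weeks, T1 at 12 weeks, T2 at 6 months, Late scan after T2, two-sided 5% tests, 300 per arm with 10% withdrawal, so 300 x 0.9 = 270 per arm.

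**Assumed inputs (not in the protocol).** Equal SD at both visits and in both arms, within-arm correlation rho between visits, and an Early-minus-Late gap at the first visit in SD units. These are shown as ranges.

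**The plan's own figures.** Section 12.7 gives power only for the primary chi-squared test. With 270 per arm, proportions symmetric about 50% (an assumption, as no control rate is stated) and a continuity-corrected normal approximation, differences of 25, 20, 15 and 10 points give 99.99%, 99.6%, 92.7% and 61.0%. The protocol states more than 99%, 99.6%, 93% and 61%. With 90 per arm in a stratum and alpha 0.05/3, the result is 79.9% against 80%. The figures reproduce, which supports 270 per arm as the working size. The protocol states no figure for the ANCOVA.

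**Formula.** With equal SDs the within-arm slope of the second value on the first is rho. Hence:

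- ANCOVA arm coefficient = gap2 - rho x gap1
- true difference in change = gap2 - gap1
- discrepancy = (1 - rho) x gap1

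The discrepancy is zero if gap1 = 0 or rho = 1.

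**T1 to T2, Early advantage merely persists (gap2 = gap1).** The true difference in change is 0 and ANCOVA returns (1 - rho) x gap. Simulation, 1,000 trials per setting, 270 per arm:

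| Gap at T1 (SD) | rho | Expected coefficient (SD) | ANCOVA rejects | Change score rejects |
|---|---|---|---|---|
| 0 | 0.5 / 0.7 / 0.9 | 0 / 0 / 0 | 5.9% / 5.4% / 5.7% | 5.0% / 5.1% / 5.8% |
| 0.2 | 0.5 / 0.7 / 0.9 | 0.10 / 0.06 / 0.02 | 26% / 16% / 8% | 4.8% / 5.1% / 5.6% |
| 0.5 | 0.5 / 0.7 / 0.9 | 0.25 / 0.15 / 0.05 | 89% / 66% / 25% | 4.6% / 6.5% / 5.9% |

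Hand check for gap 0.5, rho 0.5: residual variance 1 - 0.25 = 0.75; N x variance of the arm indicator = 540 x 0.25 = 135; share of T1 variance explained by arm = 0.0625/1.0625 = 0.0588; SE = sqrt(0.75/(135 x 0.9412)) = 0.077; z = 0.25/0.077 = 3.25; power about Phi(3.25 - 1.96) = 90%, in line with the simulated 89%.

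With a larger assumed gap of 1 SD (15 points, SD 15) and rho of 0.4, 0.6 and 0.8, the coefficient is +9, +6 and +3 points, with rejection in 100%, 100% and 93% of trials against 5-6% for change scores.

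**Binary version.** A 25-point difference in proportions (the effect assumed in section 12.7 for the primary variable), held constant from T1 to T2, gives a conditional odds ratio of about 2.1, 2.0 and 1.8 at latent rho 0.5, 0.7 and 0.9, with rejection in 97%, 92% and 70% of trials. A constant 10-point difference gives an odds ratio of about 1.3 and 34%, 28% and 18%.

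**T1 to T3 and T2 to T3, Late arm fully catches up (gap2 = 0).** The true difference in change is -gap and ANCOVA returns -rho x gap. For a gap of 0.5 SD this is -0.25, -0.35 and -0.45 at rho 0.5, 0.7 and 0.9, instead of -0.50: too small, with the correct sign.

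**Pairs starting at T0.** A true effect of 0.50 SD was recovered as 0.50 to 0.51, and rejection with no effect was 4.5% to 6.4%. The rule works as intended here.

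**The case against.** The protocol never lists the pairs of visits. For confidence and AD likelihood, the first measurement can be read as T0, and the SAP may say so. The cross-sectional tests and the mixed model are planned as well, so nobody need rely on the ANCOVA alone. All this carries weight: the T1 and T2 pairs are the natural reading of the text taken together, not an explicit statement, and the companion analyses lessen the harm. But the covariate rule is written out twice, and the mixed model is an addition to it, not a replacement.

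Four stronger readings are tempting and are not supported.

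- A reader might infer that every pair reports a difference that does not exist. That fits only T1 to T2. The Late scan falls between T2 and T3, so a real difference in change is expected for pairs ending at T3.
- A reader might infer an effect of the wrong sign, or apparent harm from early PET at T3. Under full catch-up the sign is right, and the planned T3 comparison addresses the level at T3 directly. The formula reverses the sign only if catch-up is partial, with gap2/gap1 between rho and 1, and the documents give no figure on which to assume that.
- A reader might take the rejection rates near 100% as typical. They rest on an assumed 1-SD gap.
- A reader might call diagnostic confidence the main longitudinal endpoint, or say the management plan is certainly tested by this rule. The secondary endpoints are not ranked, and the management endpoint counts participants with changes, so a cross-sectional test is an equally natural reading.

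**Conclusion.** The concern holds for change pairs that start at T1 or T2. There the arm coefficient differs from the arm difference in change by (1 - rho) times the gap at the first visit. For T1 to T2, an advantage that only persists would be declared a further effect in about 8% to 89% of trials instead of 5%, over assumed gaps of 0.2 to 0.5 SD and rho of 0.5 to 0.9 with 270 per arm, and more often with a larger gap. For T1 to T3 and T2 to T3, full catch-up by the Late arm is shrunk by the factor rho. If PET has no effect at the first visit there is no bias, so the rule does not create a PET effect from nothing; it misstates the timing or size of a real one. For AD likelihood the mean gap may be smaller, because positive and negative scans can move it in opposite directions.

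The affected analyses are secondary and unranked. The primary chi-squared test does not use this model. The rule should be corrected before analysis, but it does not threaten the trial's main conclusion.

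**What to change.** In section 12.6.1 and the matching synopsis bullet:

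- Name the T0 value as the covariate for T1, T2 and T3 wherever T0 is recorded (confidence, AD likelihood, patient-related outcomes at the visits where they are measured).
- Take the T1 to T2, T1 to T3 and T2 to T3 arm contrasts from the mixed-effects model already planned, with arm-by-visit terms, or from change scores not conditioned on T1 or T2. Adjusting a change score for T0 is acceptable.
- For the management plan, which has no T0 value, compare the arms at each visit, or compare change without conditioning on T1.

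The cost is a few sentences in two places, mirrored in the SAP. It needs no new data, visits or participants.

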#### 10.2.1.3 Expected adverse drug reactions

Please see the SmPC for the possible side effects of NeuraCeq™ [NeuraCeq™ SmPC] and VizamyI™ [VizamyI SmPC] and the Investigator Brochure for Flutemetamol ( $^{18}\text{F}$ ) Injection [ $^{18}\text{F}$  Flutemetamol].

These radiopharmaceuticals will deliver low amounts of ionizing radiation associated with the least risk of cancer and hereditary abnormalities.

However, AEs from the radioactive dose are not expected, since the applied radiation doses are far below doses that can cause acute effects in human tissues.

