#### **12.6.1.2 Patient Management**

- The difference between arms (Early Amyloid PET arm, the Late Amyloid PET arm, or the Free Choice arm) in the number of patients randomised to disease-modifying drug (DMD) or any other AD clinical trial at T2.
- The difference between the Early Amyloid PET arm and the Late Amyloid PET arm in number of participants with changes in the management plan (changes in or start of a new program or pharmacologic treatment) at T1 vs T2 vs T3.

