### 12.6.2 Safety variables and analyses

#### 12.6.2.1 Adverse events

- The number and percentage of participants with 1 or more AEs within 48 hours of drug administration will be summarised for the Safety Analysis Set and separately by gender, age, study arms, and strata (SCD plus, MCI, and dementia) and by IMP ( $[^{18}\text{F}]$ florbetaben vs  $[^{18}\text{F}]$ flutemetamol).
- A difference among the 3 study arms and between Early and Late Amyloid PET arms in number of AEs at 48 hours after IMP administration will be tested by means of a chi-squared test with significance level of .05. The analysis will be repeated for the safety end-point SAEs at 30 days after IMP administration.

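### Wald intervals as the default for binary secondary endpoints perform poorly at low event rates, chiefly for entry into another AD trial by T2

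*Protocol*

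**What the plan says.** - **Interval.** Protocol section 12.6.1 (Secondary efficacy variables) sets the default: "Point estimates will be presented together with 95% Wald confidence intervals". The next sentence adds: "A 95% non-parametric confidence interval will be constructed if the estimate is non-normal". It does not say how non-normality of an estimate is judged or which non-parametric method is meant. The synopsis carries the same rule under its secondary efficacy analyses.
- **Test.** The same section prescribes "a chi-squared test if the endpoint is dichotomous".
- **Endpoint most affected.** Section 12.6.1.2 compares the three arms "in the number of patients randomised to disease-modifying drug (DMD) or any other AD clinical trial at T2". No expected rate is given.
- **Timing.** Section 9.6 places the Late-arm study scan after the T2 visit, while the Early arm is scanned within 4 weeks of baseline.
- **Safety.** Section 12.6.2.1 says that differences in 48-hour AEs "will be tested by means of a chi-squared test with significance level of .05" and repeats this for 30-day SAEs. Section 12.6.2 names no confidence interval.

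**The concern.** A Wald interval takes its width from the estimated variance p(1-p)/n. When p is close to zero that estimate is itself unstable, and with no events it is exactly zero, so the interval runs from 0% to 0% as if the rate were known.

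Trial entry by T2 could plausibly behave this way. At T2 the Late arm has not had its study scan and the Early arm has. If amyloid status drives trial entry, the contrast of interest is a low rate against a near-zero one, which is where the Wald interval for a difference is weakest. What is at stake is the reported precision of a secondary endpoint, not the primary conclusion.

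**Working it through.** **1. Number per arm.** Section 12.7 gives 300 per arm and 10% withdrawal: 300 × 0.9 = 270. The protocol states no operating characteristic for the intervals, but its power figures confirm 270 as the analysed number. They use a two-proportion normal approximation with continuity correction and rates centred on 50% (the centring is an assumption). For a 10-point difference:

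power = Φ[(0.10 − 1/270 − 1.96 × √(2 × 0.25/270)) / √(2 × 0.45 × 0.55/270)] = Φ[(0.1000 − 0.0037 − 0.0843)/0.0428] = Φ(0.279) = 61.0%, as stated.

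The 15- and 20-point figures come out at 92.7% and 99.6% (stated: 93% and 99.6%). The 10% refers to the 12-week endpoint; carrying it over to T2 is a further assumption.

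**2. Zero events.** Wald for 0/270: 0 ± 1.96 × √(0 × 1/270) = 0% to 0%. The exact (Clopper-Pearson) upper limit is 1 − 0.025^(1/270) = 1.36%. The Wilson upper limit is z²/(n + z²) = 3.84/273.84 = 1.40%.

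**3. Single-arm coverage, n = 270.** Coverage is the sum of binomial probabilities over the counts whose interval contains the true rate. At a true 0.5%, the Wald interval contains 0.5% only for counts 1 to 6. Zero events alone has probability 0.995^270 = 25.8% and always misses. All rates below are assumed.

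| True rate | P(0 events) | Wald | Wilson |
|---|---|---|---|
| 0.5% | 26% | 74% | 95% |
| 1% | 6.6% | 93% | 94% |
| 2% | 0.4% | 90% | 95% |
| 3% | <0.1% | 90% | 95% |
| 5% | ~0 | 92% | 95% |

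**4. Coverage for a difference, n = 270 per arm.** The Wald interval is d ± 1.96 × √(p₁(1−p₁)/n + p₂(1−p₂)/n). If one arm's true rate is 0% it always has no events and adds no variance, so coverage equals the single-arm figure for the other arm.

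| True rates | Wald | Newcombe |
|---|---|---|
| 0% vs 2% | 90% | 99% |
| 0% vs 3% | 90% | 98% |
| 0.2% vs 1% | 92.7% | 98.9% |
| 0.5% vs 2% | 93.6% | 96.8% |
| 1% vs 3% | 94.5% | 96.3% |
| 2% vs 5% | 94.9% | 95.7% |
| 0.5% vs 0.5% | 97.5% | 99.3% |
| 1% vs 1% | 95.4% | 97.4% |
| 3% vs 3% | 94.9% | 95.7% |

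A zero-width interval for the difference needs no events in either arm: 6.7% probability at 0.5% in both arms, 0.4% at 1%.

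**5. What the change does to a result.** Take 5/270 against 0/270, a difference of 1.85 points.
- Wald: 1.85 ± 1.96 × √(0.0185 × 0.9815/270) × 100 = 1.85 ± 1.61, or 0.24 to 3.46 points.
- Newcombe: the Wilson limits are 0.79% to 4.26% and 0% to 1.40%. The lower limit is 1.85 − √((1.85 − 0.79)² + 1.40²) = 0.09. The upper limit is 1.85 + (4.26 − 1.85) = 4.26.

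**6. Chi-squared test.** The true two-sided size at a nominal 5%, 270 per arm, is 0.3%, 2.5%, 4.6%, 4.8% and 5.1% at common rates of 0.2%, 0.5%, 1%, 2% and 3%. For three arms of 270 it reaches at most 4.9%. With unequal groups (290 against 100 to 240, assumed) it reaches at most 5.2%.

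**The case against.** **Wald is only a default.** The protocol provides a fallback, and an undefined fallback is not the same as a failing one. That stands in part: Wald is not imposed without exception. But with no trigger or method a reader cannot tell when it applies, and one natural choice, the percentile bootstrap, also gives zero width at zero events.

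**Rarity is not documented.** This stands. No rate is given for trial entry. Around 3% or more in both arms, the Wald interval for a difference is near nominal. The 90% figure needs a true 0% in one arm, and Late-arm participants may still have other investigations or enter a trial without a study scan.

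**The endpoint is a difference between arms.** Also fair. The single-arm figures matter only where arm-specific rates are reported with intervals, and zero width for a difference needs 0 against 0.

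**This is detail for the analysis plan.** Section 12.1 defers details to a SAP. But the protocol names the Wald interval itself, and section 12.11 treats departures from the outlined analysis as deviations to be reported, so this is a stated choice and not silence.

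Three stronger readings are tempting and are not supported:
- *That Wald intervals are also fixed for AEs and SAEs.* The sentence belongs to secondary efficacy, and section 12.6.2 sets no interval. The remark that "AEs from the radioactive dose are not expected" concerns radiation only and is not a forecast of the overall AE rate.
- *That the problem is worst within strata.* Coverage is lower at 90 per arm, but the stratum-level tests in section 12.5.2 are for the primary endpoint. No stratum-level comparison of trial entry is stated, and strata enter the AE analysis only descriptively.
- *That chi-squared p-values are too small.* With 4 against 0 events at 270 per arm, chi-squared gives p = 0.045 and Fisher 0.124. The gap reflects Fisher's conservatism: the chi-squared test's true size stays at or below about 5% and is far below it at the lowest rates.

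**Conclusion.** The concern holds in a limited form. The default interval for binary secondary efficacy endpoints is a poor choice at low event rates, and the stated fallback does not reliably repair it. The practical exposure is mainly the trial-entry endpoint at T2. For the between-arm difference, the shortfall is about 5 percentage points of coverage against a zero-rate arm, 0 to 2 points for other unequal low rates, and essentially none for equal rates. For single-arm rates it ranges from a few points to about 20 at 0.5%, with a meaningless zero-width interval when no events occur.

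This rests on assumed rates of about 0.2% to 5%, 270 analysed per arm, and the fallback either not being invoked or giving a similar interval. It is a minor point. The primary analysis is unaffected, and no error is shown in the tests.

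**What to change.** In section 12.6.1 and the matching synopsis text, for dichotomous secondary endpoints replace Wald with Wilson score intervals for single proportions and Newcombe or Miettinen-Nurminen intervals for differences. For other endpoints, keep the present rule but name the trigger and the non-parametric method.

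The cost is a sentence in an amendment, or in the SAP with the departure recorded under section 12.11, and standard software options. The intervals become somewhat wider and at very low rates conservative (98% to 99% coverage in the 0% against 2% or 3% cases). Wilson is not perfect either. At a true 0.2% it covers only counts of 0 and 1, with probability 58.2% + 31.5% = about 90%, against 42% for Wald.

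Fisher's exact test for sparse tables is optional. It trades power for a conditional guarantee and is not needed to correct an error.
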